#### Randomisation and group allocation

To ensure allocation concealment, participants will be allocated 1:1 to either intervention or control arms using a web-based randomisation service supported by the Peninsula Clinical Trials Unit (PenCTU). We will use minimisation procedures to ensure balance between groups on two variables: time since stroke (≤3 vs >3 months), since spontaneous recovery might be more likely among those whose stroke was relatively recent,^28^ and level of functional disability (modified Rankin Scale^29^ (mRS) score ≤2 vs >2), since this may limit the extent and nature of training possible for a participant. Once the remote randomisation service has registered and randomised the participant, allocation will be made known to the trial manager, who will not be involved in assessing patient outcomes. Following randomisation, the trial manager will contact participants to inform them of group allocation.

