#### Sample size

The target recruitment number is 48 participants (24 per group). This number is based on the recommendation of 30 complete data sets for pilot studies in order to estimate outcome variance^27^ and running the intervention three times (Exeter I and South Devon, then Exeter II, ie, 3×8 patients) to enable investigation of variations in context and other process variables. This recruited number also allows estimation of a predicted attrition rate of 20% with a precision of ±5% with 95% certainty.

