#### Intervention

ReTrain is a specified intervention that is based on ARNI but also draws on poststroke exercise guidelines,^9^ our preliminary studies and stakeholder consultations; this combination makes it a novel intervention compared with other community exercise-based programmes. ReTrain aims to (1) enhance function through (A) task-related practice, (B) teaching adapted or compensatory strategies and (C) provide targeted strength training (cardiovascular physical fitness gains also occur through these activities); (2) develop self-management skills for ongoing rehabilitation; (3) personalise training using negotiated goals; and (4) instil a commitment to and habit of regular exercise for health improvement and longer term maintenance (once structured training programme has been completed). ReTrain focuses on functional mobility which includes safe and efficient walking in varied terrains, kerbs, cambers and in crowds, turning and moving quickly, climbing steps and stairs without rails, getting to and from the floor without furniture or other aids, and moving about without mobility aids or while carrying loads. Training will be based on an Intervention Delivery manual and led by personal trainers on the Register of Exercise Professionals (level 3 or above) who are ARNI-trained and accredited (and will be aware if there are stroke-related concerns that require referral) and they will have received additional training in the delivery of ReTrain. There will be a maximum ratio of one trainer to four stroke survivors. The use of personal trainers rather than clinicians is based on a principle of de-medicalising the rehabilitation process^18^
^31^
^32^ and received strong support from our SUG. It may also have cost-effectiveness benefits.^14^

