^33^ ReTrain is predominantly based in a community centre with twice weekly, 90 min sessions over 3 months, comprising: (1) an introductory one-to-one session (as a home visit); (2) group classes with up to two trainers and eight clients (preserving the maximum ratio of one trainer to four participants); (3) a closing one-to-one session (as a home visit). This is followed by three drop-in sessions over the subsequent 3 months at the community centre. The final one-to-one session and monthly drop-in sessions address concerns raised by our preliminary study participants of the sudden cessation of support.^23^ A more thorough description of the intervention can be seen in figure 2. The ReTrain Trainer and Intervention Delivery manuals were designed using an overarching theoretical framework that enabled existing evidence-based components (from the physiology of exercise training, Behaviour Change Techniques^34^ and stroke rehabilitation guidelines) to be mapped together with the as yet unresearched ARNI principles and techniques. The theoretical framework is known as the Information-Motivation-Behavioural Skills model^35^ and enables intervention mapping to take place.^36^ This mapping process will be developed and refined as part of the feasibility work of this study and will specify the essential resources, activities and behaviours of trainers and clients that must be present in sessions and across the programme. Session checklists will capture the main content and indicate where flexibility is permitted (for individualisation of training) and allow evaluation of intervention fidelity.

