#### Foreseen difficulties

(1) ‘Exercise’ as a term may be off-putting to some people. Our SUG and preliminary studies participants strongly advised that we emphasise the potential functional and quality of life benefits and not promote ReTrain as an exercise programme; however, it was agreed that community leisure centres were an acceptable venue. (2) Timing: some of those who give consent to take part may have to wait until the next ReTrain programme is ready to start. The wait will be minimised by running successive Exeter-based programmes alongside the South Devon programme and the study team will maintain brief but regular contact with those waiting. The feasibility and acceptability of this process, including the wait time and recruitment/retention issues more generally, are part of what is being tested in this pilot study. (3) Participant burden: particularly completion of the battery of measures and travel to intervention venue. These were deemed acceptable by most participants in our preliminary studies and this was affirmed during our SUG events when planning this proposal. Participant carers may experience some burden as they may need to support the participants by providing travel to and from the 23 training sessions at the community centre venue. The carer will also be asked to complete a questionnaire at two time points during the research. (4) Trainer availability: we worked with five trainers during our preliminary studies and there are currently more than 100 accredited ARNI trainers in the UK, indicating there would be capacity to deliver a future multicentre trial but more trainers might be needed if wider future implementation was indicated. Three local trainers have agreed to deliver the current study ReTrain programmes.

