#### Data analysis

Given the feasibility objectives of this pilot study, the focus of data analysis will be descriptive. For both recruitment settings (Exeter and South Devon) participant flow will be summarised using the CONSORT flow diagram, reporting recruitment and attrition rates (both treatment and study drop-outs) with 95% CIs. The diagram will also reflect the number of recruitment letters sent, numbers consenting, number randomised, number undertaking intervention and number of completed outcomes alongside means and SDs regarding the number, length and frequency of sessions. All protocol deviations, along with reasons and number of missing items on questionnaires will be reported. Mean and SDs (or equivalent) for all clinical outcomes for both study arms will be reported at baseline, 6 and 9 months follow-up. For the trial process evaluation, we will use a thematic analysis for the qualitative interview data and use several of the quantitative measures (including demographic, medical and questionnaire data) to help identify and understand potential mediators and moderators of trial outcome. For the analysis of intervention fidelity, we will use the procedures we designed and tested in our preliminary studies for the video analysis combined with trainer interview data and the session checklists (that will be part of the Intervention Delivery manual). These data collection and analysis methods will be assessed for their potential to inform the process evaluation component of a definitive trial. In such a future trial, the health economics analysis will be a cost-utility analysis, using QALYs and secondary analyses will investigate the benefits of the intervention more broadly within the framework of a cost consequences approach, so offering the potential to weight different outcomes in a multicriteria decision analysis framework.^51^ In this pilot study, we will assess the relative benefits of calculating health-related quality of life using SF-6D developed from the SF-12 over the QALY calculated using EQ-5D-5L; explore the psychometric properties of the SF-12 and investigate whether it has greater ability to discriminate between the milder health states. We will assess costs associated with intervention delivery as well as assess the feasibility of collecting health and social service resource use through a Service Receipt Inventory. Any missing data in the Inventory will be recorded and we will check if any resource use categories are misunderstood by matching Inventory completion with medical records for a subgroup of participants. This will help us develop strategies to minimise missing data in a future definitive trial.

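### Minimisation leaves out site and programme, so nothing holds ReTrain allocations near the eight places that each programme offers

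*Protocol article*

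**What the plan says.** Under Randomisation and group allocation, the protocol article says: "We will use minimisation procedures to ensure balance between groups on two variables". The two are time since stroke (cut at 3 months) and modified Rankin score (cut at 2). The list is closed and contains neither site nor programme.

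Under Sample size, 48 participants are planned, 24 per group, on the basis of "running the intervention three times (Exeter I and South Devon, then Exeter II, ie, 3×8 patients". South Devon therefore has one programme and Exeter has two.

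Under Intervention, the programme consists mainly of "group classes with up to two trainers and eight clients". The limit behind this is also stated: "There will be a maximum ratio of one trainer to four stroke survivors". Under Foreseen difficulties: "Three local trainers have agreed to deliver the current study ReTrain programmes". The same section says that the Exeter programmes will run alongside the South Devon one, so recruitment in the two areas overlaps.

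Waiting is foreseen under Participant recruitment and Foreseen difficulties, either until a group of eight is ready or until the next programme starts. The text shown does not say what happens when more than eight people in one programme are allocated to ReTrain.

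Under Data analysis: "For both recruitment settings (Exeter and South Devon) participant flow will be summarised using the CONSORT flow diagram", with attrition covering both treatment and study drop-outs.

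**The concern.** Minimisation over the whole trial can balance the arms well overall while leaving each area unbalanced. When two areas recruit at the same time into one minimisation, the South Devon participants are close to a random subset of a balanced sequence. The two stated factors do almost nothing to keep that subset at 8:8.

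This matters because the places are fixed and fully used. A ninth ReTrain allocation in Exeter I would have to wait for Exeter II. A ninth in South Devon has no later programme in that area. Too few allocations leave a group below eight, which changes the group format under test.

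The pilot exists to measure retention, acceptability and deliverability. A person who waits long or never starts because the class was full says something about the allocation rule, not about ReTrain. With 24 in the arm, one or two such people are 1/24 = 4% to 2/24 = 8% of it.

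**Working it through.** **The plan's own figure.** 3 programmes × 8 places = 24 ReTrain participants; doubled for 1:1 allocation, 48. This reproduces the stated total. It also shows that places (South Devon 8, Exeter 16) equal planned ReTrain allocations. Any area split other than exactly 8 and 16 puts one area over its places.

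**Inputs from the article:** 48 participants, 1:1, two minimisation factors, three programmes with at most eight clients each, Exeter and South Devon overlapping.

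**Assumptions not in the article:** 16 recruits per programme (48/3); 10-30% at 3 months or less since stroke; 40-50% in one Rankin category; the preferred arm chosen with probability 1 (deterministic) or 0.8 (biased coin); arrival order.

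**Exact benchmark: allocation unrelated to site, 24 of 48 to ReTrain.** Let X be the South Devon ReTrain count.

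- P(X = x) = C(16,x)·C(32,24−x)/C(48,24).
- P(X = 8) = 0.24; P(X > 8) = 0.38; P(X < 8) = 0.38.
- P(one area over its places) = 1 − 0.24 = 0.76.
- P(all three programmes exactly 8) = 0.240 × C(16,8)²/C(32,16) = 0.240 × 0.276 = 0.066. The total is 24, so any other split puts some programme over 8: 1 − 0.066 = 0.93.
- With 12 or 20 South Devon recruits instead of 16, P(one area over its places) = 0.89 or 0.88.

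**Simulated minimisation on the two stated factors, 16 recruits per programme.**

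| Recruitment | Rule | South Devon >8 | One area over its places | Some programme >8 |
|---|---|---|---|---|
| Exeter I and South Devon interleaved, then Exeter II | deterministic | about 37% | about 73% | about 78% |
| same | 80% coin | about 37% | about 74% | about 85% |
| strictly sequential | deterministic | 13-14% | about 30% | about 30% |
| strictly sequential | 80% coin | 28-30% | 59-63% | about 68% |

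With overlap, South Devon reaches 10 or more in about 15% of trials. For comparison, simple randomisation of 16 people gives P(>8) = 40%, so the two factors barely improve on it. The largest group has a median of 9 and a 90th percentile of 10.

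**Same measure after the change (some programme >8, overlapping recruitment).**

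| Scheme | Deterministic | 80% coin |
|---|---|---|
| Two factors as stated | about 78% | about 85% |
| Programme added, equal weight | 16-23% | about 58% |
| Programme added, triple weight | about 1% | about 41% |
| Exactly 8 of 16 per programme | 0% | 0% |

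With triple weight, the chance of 10 or more in a programme is about 3% or less under either rule.

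**The case against.** The strongest reply is that the size of the problem rests on things the article does not state. It sets no quota of 16 per programme, recruitment is rolling, and a site that stopped randomising after its eighth ReTrain allocation would never overflow. The figure showing one cohort's flow is not available, and such mechanics may sit in the full protocol. Recruitment order matters too: strictly sequential cohorts with deterministic minimisation bring the chance down to about 30%. These points limit the number. They do not remove the concern, because the article describes overlapping programmes and states no limit on allocations by site.

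A reader might also infer more than the documents support:

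- **That South Devon itself will probably be over-filled.** It is about 37%, and under-filling is equally likely. The high figures refer to some programme or either area.
- **That surplus participants go untreated.** Exeter I surplus can join Exeter II, and the article plans for people waiting. Travel costs are offered, and nothing rules out a South Devon participant attending in Exeter. Non-delivery is possible, not shown.
- **That only the ReTrain arm waits.** The article describes waits after consent and does not say whether randomisation comes before or after them.
- **That treatment drop-out will be inflated by a known amount.** This is not quantified, and the flow diagram reports the number randomised and the number undertaking the intervention separately, so a person without a place could be seen.
- **That arm and setting are seriously confounded.** Only participant flow is split by setting, the analysis is descriptive, and the article disclaims power to compare arms. A 9:7 split in one area matters little.

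**Conclusion.** The concern holds in a limited form. The stated minimisation does nothing to keep ReTrain allocations near eight per programme, in a design with exactly 24 places for 24 planned participants and a single South Devon programme. Under overlapping recruitment with 16 recruits per programme, some programme exceeds eight in about 78-85% of trials and one area exceeds its places in about 73-74%. Under strictly sequential recruitment, some programme exceeds eight in about 30-68%.

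The excess is usually one or two people. The consequence is avoidable waits, under-filled groups or possible non-delivery, which would blur the feasibility and treatment drop-out figures. It does not threaten the validity of the pilot. The change is worth making because it is cheap and lowers the risk in every scenario examined.

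**What to change.** Either of two changes would serve.

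1. **Add programme (Exeter I, South Devon, Exeter II) as a third minimisation factor with a heavy weight.** This is a change to the existing web-based service and needs no extra participants or visits. The cost is somewhat greater predictability of allocation, which matters because allocation concealment is one of the procedures that the pilot tests. A random element limits that predictability but leaves about a 41% chance that some programme exceeds eight.
2. **Randomise each programme's participants together as one balanced 8:8 set once all have consented.** Balance is then exact, and there are no predictable last allocations because all are drawn at once. The cost is a wait between consent and allocation, which falls on both arms.

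If a random element is kept, the protocol also needs a statement on surplus allocations. The authors must reconcile how a ninth ReTrain allocation fits the stated group maximum, in particular in South Devon.

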#### Blinding

Participants, personal trainers providing the intervention, and researchers conducting the process and economic evaluation cannot be blinded to allocation. However, outcomes will be assessed by an independent assessor blinded to group allocation. Participants, who have been informed of their allocation, will be reminded to hide their allocation from the assessor. Any incidents of unblinding will be recorded, and the assessor will be asked to record their guess of participant allocation after undertaking the assessments. Following recommended strategies to maintain and assess blinding,^30^ the outcomes assessor will not be based at the research centre.

#### Intervention

ReTrain is a specified intervention that is based on ARNI but also draws on poststroke exercise guidelines,^9^ our preliminary studies and stakeholder consultations; this combination makes it a novel intervention compared with other community exercise-based programmes. ReTrain aims to (1) enhance function through (A) task-related practice, (B) teaching adapted or compensatory strategies and (C) provide targeted strength training (cardiovascular physical fitness gains also occur through these activities); (2) develop self-management skills for ongoing rehabilitation; (3) personalise training using negotiated goals; and (4) instil a commitment to and habit of regular exercise for health improvement and longer term maintenance (once structured training programme has been completed). ReTrain focuses on functional mobility which includes safe and efficient walking in varied terrains, kerbs, cambers and in crowds, turning and moving quickly, climbing steps and stairs without rails, getting to and from the floor without furniture or other aids, and moving about without mobility aids or while carrying loads. Training will be based on an Intervention Delivery manual and led by personal trainers on the Register of Exercise Professionals (level 3 or above) who are ARNI-trained and accredited (and will be aware if there are stroke-related concerns that require referral) and they will have received additional training in the delivery of ReTrain. There will be a maximum ratio of one trainer to four stroke survivors. The use of personal trainers rather than clinicians is based on a principle of de-medicalising the rehabilitation process^18^
^31^
^32^ and received strong support from our SUG. It may also have cost-effectiveness benefits.^14^
^33^ ReTrain is predominantly based in a community centre with twice weekly, 90 min sessions over 3 months, comprising: (1) an introductory one-to-one session (as a home visit); (2) group classes with up to two trainers and eight clients (preserving the maximum ratio of one trainer to four participants); (3) a closing one-to-one session (as a home visit). This is followed by three drop-in sessions over the subsequent 3 months at the community centre. The final one-to-one session and monthly drop-in sessions address concerns raised by our preliminary study participants of the sudden cessation of support.^23^ A more thorough description of the intervention can be seen in figure 2. The ReTrain Trainer and Intervention Delivery manuals were designed using an overarching theoretical framework that enabled existing evidence-based components (from the physiology of exercise training, Behaviour Change Techniques^34^ and stroke rehabilitation guidelines) to be mapped together with the as yet unresearched ARNI principles and techniques. The theoretical framework is known as the Information-Motivation-Behavioural Skills model^35^ and enables intervention mapping to take place.^36^ This mapping process will be developed and refined as part of the feasibility work of this study and will specify the essential resources, activities and behaviours of trainers and clients that must be present in sessions and across the programme. Session checklists will capture the main content and indicate where flexibility is permitted (for individualisation of training) and allow evaluation of intervention fidelity.

**Figure 2 BMJOPEN2016012375F2:**
[figure not shown]
The ReTrain programme. (ARNI, Action for Rehabilitation from Neurological Injury; GP, general practitioner; TM, trial manager).

##### Links between ARNI and ReTrain

The ARNI principles were identified through analysis of ARNI documentation,^18^ discussion with its developer and the survey of existing ARNI programmes. Although ARNI aims to address all aspects of function, the ReTrain programme focuses on functional mobility because of its association with independence in activities of daily living and social participation. ARNI provides strategies for developing these skills that have been adapted for people with hemiplegia and other stroke-related impairments. ReTrain will not focus on upper limb function except in the service of such mobility tasks.

ARNI aims to enhance individual's ability to manage their own rehabilitation and exercise programme. This is achieved through a variety of strategies and techniques including education in exercise principles after stroke, developing skills in goal setting, functional problem solving and self-monitoring, and establishing a programme of regular independent home-based exercise. ReTrain will ensure that these activities are incorporated into the training process.

ARNI is designed as a personalised programme with substantial one-to-one training to ensure individual tailoring of activities, feedback and progression, and encouragement to work at the edge of personal capacity. The ReTrain programme combines these features with the benefits of a group programme which include peer support, pair work and efficient use of resources.^22^
^23^ The structure of the ReTrain programme is described in figure 2, and a more detailed Intervention Delivery manual will be developed and refined as part of the study.

